## 2.4 Potential Risks and Benefits

### 2.4.1 Potential Risks

Due to its mode of action, bleeding may occur during ancrod treatment. The direct effect of ancrod on the coagulation cascade and on platelet function may cause microscopic hematuria, bleeding at puncture sites, bruising and, in rare cases, melena, epistaxis, and hematemesis (Latallo, 1983). Many bleeding adverse events are related to bruising and are of limited clinical significance. The

|                                |                             |                      |
|--------------------------------|-----------------------------|----------------------|
| Protocol Amendment 7.1         | Study no.: NM-V-101         | Page 23 of 85 |
| Date of Amendment: 15 Feb 2018 | EudraCT No.: 2012-000066-37 |                      |

bleeding risk appears to be increased when fibrinogen levels remained below 40 mg/dL for longer periods.

The relatively high incidence of adverse events observed in clinical studies in patients with acute ischemic stroke treated with ancrod may be attributed to advanced age, predisposition, and vulnerability of this patient population and cannot be extrapolated to patients with sudden hearing loss who will be treated with a different, moderate dosing regimen. Further, the incidence of adverse events observed in the direct comparison of defibrinogenation therapy with corticosteroid revealed no minor or major bleeding. Side effects were observed in 84.9% of patients who received defibrinogenation therapy and in 85.9% of patients who received corticosteroid treatment (Kubo et al., 1988).

Local reactions, such as urticaria and exanthema, are rare but may occur after subcutaneous use. Some patients who had received ancrod subcutaneously developed local irritation or itching. These skin reactions have responded to antihistamine therapy. There was no evidence of an allergic reaction in healthy subjects or in patients treated with ancrod repeatedly. Nevertheless, special attention should be paid to patients receiving a second course of ancrod because neutralizing antibodies may occur particularly after long-term subcutaneous administration.

In this placebo-controlled study one third of patients are receiving inactive drug which may be a reason for the lack of efficacy. In such cases where symptoms of the disease are unchanged or aggravated, the patient is allowed to switch on day 8 to corticosteroid treatment, vasodilators, vitamin C, vitamin B12 or antihistamines if deemed necessary at the discretion of the investigator.

#### **2.4.2 Potential Benefits**

The therapeutic value of the frequently used oral or intratympanal steroids for the treatment of sudden hearing loss remains unclear (Wei et al., 2006). Other presently used therapies have not been confirmed in state-of-the-art double-blind randomized clinical trials and did therefore not obtain regulatory approval. The existing treatment options for SSHL may thus be comparable to the placebo treatment arm in the planned clinical study.

In contrast, clinical data obtained from a study with batroxobin, a serine protease derived from another snake venom and with similar mode of action as ancrod revealed a good treatment effect in patients with moderate to severe hearing loss. The improvement was significantly better in patients on batroxobin than in patients receiving corticosteroid treatment.

Ancrod's therapeutic benefit lies in its fibrinogenolytic action which causes reduced plasma fibrinogen concentration, associated with a progressively reduced blood viscosity by 30-40% of the pretreatment levels (Ernst and Dormandy, 1981). The diminished viscosity leads to an

|                                |                             |                      |
|--------------------------------|-----------------------------|----------------------|
| Protocol Amendment 7.1         | Study no.: NM-V-101         | Page 24 of 85 |
| Date of Amendment: 15 Feb 2018 | EudraCT No.: 2012-000066-37 |                      |

improvement in microcirculation. These rheological changes are sustained and viscosity approaches pretreatment values approximately 10 days after termination of ancrod treatment.

The treatment of SSHL with ancrod represents a novel approach which is expected to exhibit:

- better efficacy than existing therapies
- favorable safety profile
- good patient compliance due to simple dosing regimen

Thus, for each subject, the possibility of a positive therapeutic effect and his or her contribution to the scientific understanding of the properties and actions of ancrod are the only benefits.

### **3 Design, Objectives and Endpoints**

#### **3.1 Study Design**

This is a randomized, double-blind, multi-center, placebo-controlled, parallel-group phase II proof-of-concept study comparing ancrod treatment versus placebo in patients with unilateral SSHL. The study will be conducted in approximately 20 sites in Germany, Czech Republic, Serbia and Macedonia. Study treatment and all study assessments will be performed in an outpatient setting. After obtaining informed consent, patients presenting with unilateral sudden hearing loss within 7 days after onset will be screened for eligibility. Patients meeting all in- and exclusion criteria including the screening audiometric assessments will be randomized into 2 cohorts in a ratio of 2:1 between active treatment and placebo according to a randomization code generated prior to start of patient recruitment by the data management/statistics group.

At screening, prior to administration of study drug infusion, standard air and bone pure tone audiometry (PTA) will be measured. In addition, tympanometry, stapedius reflex measurements, otoacoustic emissions and speech intelligibility test (specific national test per country to determine the dB value where 50 % of single words will be understood) will be performed. For assessment of vertigo, oculomotor function will be measured using video- or electronystagmography over 30 seconds. Frenzel goggles for the assessment of vertigo are possible as well. The occurrence and the degree of tinnitus will be determined using a numerical rating scale (NRS).

Patients will be screened and enrolled at designated clinical study sites where all test procedures are performed. All screening assessments including randomization and patient enrollment are to be performed within 36 hours. In total, 87 evaluable patients randomized in a 2:1 ratio will be needed to confirm a treatment difference of 15 dB PTA with an  $\alpha$ -level of 5% and a statistical power of 90%, assuming a standard deviation of 20%. To compensate for dropouts, a total of

|                                |                             |                      |
|--------------------------------|-----------------------------|----------------------|
| Protocol Amendment 7.1         | Study no.: NM-V-101         | Page 25 of 85 |
| Date of Amendment: 15 Feb 2018 | EudraCT No.: 2012-000066-37 |                      |

99 patients are planned to be enrolled, 66 patients on ancrod and 33 on placebo. The recruitment period will be approximately 57 months. The study duration for each patient will be 90 days.

Screening measurements (for details see Section 4.1) prior to initiation of study drug administration on Day 1 (Visit 1) will include an assessment of plasma fibrinogen concentration in the local laboratory. Immediately after randomization on Day 1 (Visit 1), patients will receive the initial infusion of investigational product. The initial dose of ancrod will be adjusted according to the screening fibrinogen concentration by using different infusion durations at a constant infusion rate (see Section 7.1).

On the following day (Day 2, Visit 2), a venous blood sample will be taken for coagulation assays (fibrinogen, thrombin time [TT], prothrombin time [PT], activated partial thromboplastin time [aPTT]) to be performed in the selected responsible laboratory (local or central) of the site within 36 hours. The investigator must announce the taking of the blood sample for fibrinogen per fax to Nordmark (Pharmaceutical Development, unblinded personnel). Thereafter, on Day 2, a weight-adjusted ancrod dose of 1 IU/kg will be administered subcutaneously. Nordmark Pharmaceutical Development has to be informed immediately in writing (fax) from the responsible laboratory or designee on the result of the coagulation assays. The result of the coagulation assay may in principle not be communicated from the laboratory to the investigator or any other blinded study personnel. If the fibrinogen concentration on Day 2 is lower than 50 mg/dl the investigator will be informed by Nordmark Pharmaceutical Development that this patient may not receive further injections of ancrod on Day 4 and Day 6. This deviation has to be documented in the dosing worksheet. All other study related activities will be performed as planned. If the fibrinogen concentration on Day 2 is  $\geq 50$  mg/dl Nordmark Pharmaceutical Development will inform the investigator that the patient may receive further subcutaneous injections of 1 IU/kg ancrod on Day 4 and Day 6 (Visits 3 and 4) (Figure 1). Regardless of the result, Nordmark Pharmaceutical Development may not communicate any values to the investigator or any other blinded study personnel.

On Day 8 (Visit 5) the treatment effect will be evaluated by means of audiometry and speech recognition, and the presence and intensity of tinnitus and vertigo will be determined. In addition, a blood sample will be taken for coagulation assays and biomarkers will be measured. The result of the coagulation assay may in principle not be communicated from the laboratory to the investigator or any other blinded study personnel. If, on Day 8 (Visit 5), no improvement of clinical signs and symptoms compared to the baseline value has been achieved, the patient will be allowed to switch to corticosteroid treatment, vasodilators, vitamin C, vitamin B12 or antihistamines if deemed necessary at the discretion of the investigator.

During the follow-up visits on Day 30 and Day 90 (Visits 6 and 7) the treatment effect will again be determined by audiometric evaluation and tinnitus intensity to monitor for signs of relapse in the affected ear. Comparison of this audiogram to the audiogram at enrollment will determine the stability of the hearing improvement after the end of treatment.

[figure not shown]

**Figure 1: Study Flow Chart**

i.v. =intravenous, s.c. =subcutaneous, SSHL = sudden sensorineural hearing loss.

## 3.2 Objectives and Endpoints

The primary objective of this study is to evaluate the efficacy of ancrod as primary treatment of SSHL compared to placebo in patients with unilateral sudden sensorineural hearing loss as determined by audiometry.

The secondary objectives of this study are to:

- Evaluate the relationship between biomarkers and clinical efficacy.
- Investigate the safety and tolerability of ancrod.

### 3.2.1 Primary Outcome Measure

The primary outcome measure of the study will be the change in PTA in the affected ear from screening (Day 1; Visit 1) until Day 8 (Visit 5). The PTA will be calculated as the arithmetic mean of air conduction thresholds at the affected consecutive frequencies in the frequency range of 0.125 to 8 kHz. A non-affected frequency within two affected frequencies will be included.

### 3.2.2 Secondary Outcome Measures

Secondary outcome measures will include:

- Change in word recognition score from screening to Day 8, Day 30 and Day 90.

|                                |                             |                      |
|--------------------------------|-----------------------------|----------------------|
| Protocol Amendment 7.1         | Study no.: NM-V-101         | Page 27 of 85 |
| Date of Amendment: 15 Feb 2018 | EudraCT No.: 2012-000066-37 |                      |

- Change of audiogram in the affected ear from screening to Day 30 and Day 90.
- Change in fibrinogen concentration from screening to Day 2 and Day 8.
- Change in biomarkers from screening to Day 8.
- Patient assessment of change in hearing impairment.
- Physician assessment of change in hearing impairment.
- Change in tinnitus severity.

## **4 Schedule of Events and Study Duration**

This section provides a detailed description of the study procedures to be performed at each visit. For an overview on study procedures please refer to the study schedule in Appendix 17.6.

### **4.1 Screening (Day 1, Visit 1)**

All screening assessments including randomization and patient enrollment are to be performed within 36 hours. Informed consent is to be obtained from each patient prior to any study-related procedures. After obtaining informed consent, the following assessments will be performed prior to initiation of study drug infusion on Day 1 (Visit 1):

- Review of inclusion/exclusion criteria.
- Review of demographic and baseline characteristics.
- General physical and otolaryngological examination including otoacoustic emissions, tympanometry, stapedius reflex measurements
- Vital signs.
- Review of medical history as well as previous medication (all medication taken within the last 30 days prior to Visit 1) and concomitant medication.
- Pregnancy test.
- Audiometric evaluation (PTA and speech intelligibility test inclusive word recognition).
- Occurrence and severity of tinnitus
- Vertigo evaluated using video- or electronystagmography or Frenzel goggles.
- Patient assessment of change in hearing impairment assessed using NRS
- Physician assessment of change in hearing impairment assessed using NRS
- Biomarkers (see Section 8.2.1).

|                                |                             |                      |
|--------------------------------|-----------------------------|----------------------|
| Protocol Amendment 7.1         | Study no.: NM-V-101         | Page 28 of 85 |
| Date of Amendment: 15 Feb 2018 | EudraCT No.: 2012-000066-37 |                      |

- Blood sample for neutralizing anti-ancrod-antibodies
- Safety laboratory assessments including coagulation, hematology, clinical chemistry, and urinalysis (for details see Section 8.2.2).

Immediately after randomization, patients will receive the initial administration of study drug (active or placebo) as intravenous infusion on the first day of treatment. The initial dose of study drug will be adjusted according to the screening fibrinogen concentration by using different infusion durations at a constant infusion rate (see Section 7.1).

All screening assessments including randomization and patient enrollment are to be completed within 36 hours.

AEs will be recorded starting from initiation of study drug infusion.

## **4.2 Visits of the Double-Blind Treatment Phase (Days 2, 4, 6 and 8)**

### **Day 2 (Visit 2)**

On the following day (Day 2, visit 2), a venous blood sample will be drawn for the determination of fibrinogen, TT, PT, and aPTT. This assay will be performed within 36 hours in the selected laboratory (local or central) of the site for reason of safety. The result of this coagulation analysis will be immediately sent to Nordmark Pharmaceutical Development. If the fibrinogen concentration on Day 2 is lower than 50 mg/dl the investigator will be informed by Nordmark Pharmaceutical Development that this patient may not receive further injections of ancrod on Day 4 and Day 6. This deviation has to be documented in the dosing worksheet. All other study related activities will be performed as planned. If the fibrinogen concentration on Day 2 is  $\geq 50$  mg/dl, Nordmark Pharmaceutical Development will inform the investigator that the patient may receive further weight adjusted subcutaneous injections of study drug at a dose of 1 IU/kg ancrod-fibrinogenase or placebo. Regardless of the result, Nordmark Pharmaceutical Development may not communicate any values to the investigators.

AEs and concomitant medication will be recorded.

### **Day 4 (Visit 3) and Day 6 (Visit 4)**

The following assessments and treatments will be done on Days 4 and 6 of the double-blind treatment phase:

- Review of concomitant medication.
- Weight adjusted subcutaneous administration of study drug (1 IU/kg ancrod-fibrinogenase or placebo).
- Recording of AEs.

|                                |                             |                      |
|--------------------------------|-----------------------------|----------------------|
| Protocol Amendment 7.1         | Study no.: NM-V-101         | Page 29 of 85 |
| Date of Amendment: 15 Feb 2018 | EudraCT No.: 2012-000066-37 |                      |

Treatments and assessments of day 4 and day 6 may be shifted to the following day, however, it must be ascertained that between the two visits there is one day without treatment.

### **Day 8 (Visit 5)**

Day 8 will be the last day of the double-blind treatment phase. The assessments of day 8 may be shifted to the previous or the following day, however, visit 4 and visit 5 are to be performed on different days.

On day 8 no study drug will be administered and the following assessments will be performed:

- General physical and otolaryngological examination including otoacoustic emissions, tympanometry, stapedius reflex measurements.
- Vital signs.
- Review of concomitant medication.
- Audiometric evaluation (PTA and word recognition).
- Presence and severity of tinnitus.
- Vertigo assessed by video- or electronystagmography or Frenzel goggles.
- Patient assessment of change in hearing impairment.
- Physician assessment of change in hearing impairment.
- Safety laboratory assessments including coagulation, hematology, clinical chemistry, and urinalysis.
- Biomarkers.
- Blood sample for neutralizing anti-ancrod-antibodies
- Recording of AEs.

### **4.3 Follow-up Visits at Day 30 and Day 90 (± one week)**

The following assessments will be done at the follow-up visits on Day 30 and Day 90:

- Review of concomitant medication.
- Audiometric evaluation (PTA and word recognition).
- Presence and severity of tinnitus.
- Patient assessment of change in hearing impairment.
- Physician assessment of change in hearing impairment.
- Recording of AEs.

|                                |                             |                      |
|--------------------------------|-----------------------------|----------------------|
| Protocol Amendment 7.1         | Study no.: NM-V-101         | Page 30 of 85 |
| Date of Amendment: 15 Feb 2018 | EudraCT No.: 2012-000066-37 |                      |

- Blood sample for neutralizing anti-ancrod-antibodies (only on Day 30)

#### **4.4 Final Study Visit at Day 90 ( $\pm$ one week)**

The follow-up visit on Day 90 will be the final study visit.

#### **4.5 Early Termination Visit**

If a patient prematurely terminates the study, a complete final examination as detailed in Section 4.2 is to be performed at the time of withdrawal. Furthermore the blood sample for determination of the neutralizing anti-ancrod antibody should be taken on day 30 ( $\pm$  one week) if possible.

#### **4.6 Unscheduled Visit**

Not applicable.

#### **4.7 Duration of the study**

This study was initiated (first patient in) in August 2013. The recruitment period is planned to be approximately 57 months. The study duration for each patient will be 90 days. The overall duration of the study is planned to be  $57 + 3 = 60$  months, with the last patient out in August 2018.

### **5 Patients**

#### **5.1 Study Population**

This study will include patients presenting with unilateral idiopathic sudden hearing loss. The criteria for defining the SSHL diagnosis, hearing loss severity, and hearing improvement will be based on pure tone air and bone conduction thresholds collected during standardized audiometric tests including standard air and bone conduction PTA, tympanometry, stapedius reflex measurements, otoacoustic emissions and speech intelligibility test (specific national test per country to determine the dB value where 50 % of single words will be understood).

It is planned to randomize a total of 99 patients to either ancrod or placebo in a 2:1 ratio (i.e. 66 patients receiving ancrod and 33 patients receiving placebo. For details on sample size determination see Section 10.1.

##### **5.1.1 Patients and Characteristics**

Patients must meet all of the inclusion and exclusion criteria as outlined in Section 5.1.2 and Section 5.1.3, to be eligible for randomization into the double-blind treatment period at the screening visit (Visit 1).

|                                |                             |                      |
|--------------------------------|-----------------------------|----------------------|
| Protocol Amendment 7.1         | Study no.: NM-V-101         | Page 31 of 85 |
| Date of Amendment: 15 Feb 2018 | EudraCT No.: 2012-000066-37 |                      |

### 5.1.2 Inclusion Criteria

The criteria for defining the SSHL diagnosis are based on pure tone air and bone conduction thresholds collected during standardized audiometric tests. Patients must meet all of the following inclusion criteria in order to be eligible for this study:

1. Unilateral idiopathic sudden sensorineural hearing loss  $\geq 30$  dB in at least 2 consecutive frequencies in the affected ear or  $\geq 20$  dB in 3 consecutive frequencies based upon evaluation of 8 frequencies, 0.125, 0.25, 0.5, 1, 2, 4, 6, and 8 kHz, compared to the contralateral ear.
2. Symmetric hearing prior to onset of SSHL, according to patient's recollection.
3. Patients with hearing loss not greater than 90dB at 0.125, 0.25, 0.5, 1, 2, 4, 6, and 8 kHz.
4. Enrollment has to be accomplished within 7 days after SSHL onset.
5. Male or female aged  $\geq 18$  to  $\leq 70$  years.
6. Women of childbearing potential who are sexually active with opposite partners have to perform adequate contraception with a combination of a highly effective method of birth control and additional barrier contraception.

[Highly effective method of birth control is defined as those, alone or in combination, that result in a low failure rate (i.e. less than 1% per year) when used consistently and correctly for the entire study duration: combined (oestrogen and gestagen) oral contraceptives, hormone implants, hormone injectables, or hormone containing intrauterine device that needed to be in place for a period of at least 2 months prior to screening. Additional barrier contraception (at least the following methods are allowed: condom of the male, diaphragm with spermicide, portio cap with spermicide) has to be used for the duration of the trial, defined as from the time of screening to at least 10 days after Day 6 (Visit 4) of the double-blind treatment phase. A single barrier method is not acceptable. Women of non-childbearing potential can be included if surgically sterile (documented complete hysterectomy or bi-tubal ligations) or post-menopausal  $>1$  year.]

7. Men of reproductive potential must use condoms. In addition, the female partner should also be on a safe hormonal contraception (e.g. combined oral contraceptives, hormone implants, hormone injectables or hormone containing intrauterine device) or use a barrier contraception (e.g. intrauterine device, diaphragm or portio cap with spermicide), if she is of childbearing potential.
8. Ability to understand and to follow the study protocol.

|                                |                             |                      |
|--------------------------------|-----------------------------|----------------------|
| Protocol Amendment 7.1         | Study no.: NM-V-101         | Page 32 of 85 |
| Date of Amendment: 15 Feb 2018 | EudraCT No.: 2012-000066-37 |                      |

### 5.1.3 Exclusion Criteria

The presence of any of the following will exclude a patient from study enrolment:

1. Pregnant or breast-feeding female.
2. positive pregnancy test before receiving study drug
3. Body weight > 140 kg
4. Bilateral SSHL.
5. Incomplete recovery after previous SSHL, when symmetric hearing was not reached again, according to patient's recollection.
6. Due to history of physical efforts suspected perilymph fistula or membrane rupture.
7. Previously existing, known retrocochlear hearing loss.
8. Any history of any ear operation or local inflammatory disease in the past one year.
9. History of blunt or penetrating ear trauma, head trauma, barotrauma, or acoustic trauma immediately preceding SSHL.
10. History of Menière's disease, autoimmune hearing loss, radiation-induced hearing loss, endolymphatic hydrops.
11. Any pre-treatment within the preceding 30 days prior to screening, ongoing treatment or planned treatment of SSHL-related hearing loss.
12. History of chronic inflammatory diseases or autoimmune diseases e.g. rheumatic disease, including rheumatoid arthritis, scleroderma, lupus erythematosus, polymyalgia rheumatica, polyarteritis nodosa, temporal/giant cell arteritis, Sjögren's syndrome, or ulcerative colitis and Crohn's disease.
13. History of unstable angina, coronary artery stenting or bypass grafting within three months of enrolment, transient ischemic attacks or stroke within four weeks of enrolment.
14. Prior chemotherapy or treatment with immunosuppressant drugs (azathioprine, chlorambucil, cyclophosphamide, or other alkylating agents), cyclosporine, etanercept, infliximab, interferon or any therapy with drugs known as ototoxic (e.g. aminoglycosides, cisplatin, loop diuretics, quinine etc.) in the past 6 months.
15. Gastrointestinal pathology: lesions liable to bleed such as active peptic ulcer disease, inflammatory bowel disease, history of gastrointestinal bleeding, or recent hemorrhage at any anatomical site requiring medical intervention.
16. Screening plasma fibrinogen level of <180 mg/dL.

|                                |                             |                      |
|--------------------------------|-----------------------------|----------------------|
| Protocol Amendment 7.1         | Study no.: NM-V-101         | Page 33 of 85 |
| Date of Amendment: 15 Feb 2018 | EudraCT No.: 2012-000066-37 |                      |

17. Known disorder of platelet function or coagulation abnormality.
18. Platelet count of  $<100,000/\text{mm}^3$ .
19. Severe liver disease.
20. Hepatic failure (e.g., aspartate aminotransferase (SGOT) or alanine aminotransferase (SGPT)  $\geq 3 \times$  upper limit of normal [ULN]).
21. Treatment with hyperbaric oxygen within one week prior to study drug.
22. Renal insufficiency (e.g., blood urea nitrogen or creatinine  $\geq 2 \times$  ULN) or patients on renal dialysis.
23. Use of another investigational drug within 30 days prior to SSL onset.
24. Any other serious medical condition that might interfere with subject evaluation over the 90-day study period, based on the investigator's judgment, e.g. planned surgical intervention or any other condition which might give doubt for non-completing the study e.g. planned holiday, distance between investigational center and place of origin.
25. Known hypersensitivity to the drug substance or excipients
26. Blood or blood product infusion within one week prior to study drug.
27. Use of any prohibited drug listed in chapter 6.4.1 and 6.4.2 of this study protocol
28. Immunoglobulin infusion 4 weeks prior to study drug
29. Planned treatment using intramuscular injections (e.g. vaccinations, vitamin B therapy)
30. Conditions associated with an increased risk of hemorrhaging such as major surgery, history of hemorrhagic stroke, intracranial hematoma, subarachnoid hemorrhage, diabetic retinopathy, retinopathy grade 3 or worse, known hemostatic disorders.
31. Uremia and renal colic with calculus, cerebrovascular accident, and history of neurosurgery
32. History of malignant hypertension and/or diastolic pressure  $> 105 \text{ mmHg}$
33. Acute pericarditis
34. Subacute bacterial endocarditis
35. Septicemic states with or without evidence of diffuse intravascular coagulation
36. History of clinically relevant immediate-type allergy (type I) with respect to e.g. mildew, (house dust) mite, cockroach, hymenoptera venom, dog, cow and honeydew melon
37. Hearing loss of infectious or oncology origin

|                                |                             |                      |
|--------------------------------|-----------------------------|----------------------|
| Protocol Amendment 7.1         | Study no.: NM-V-101         | Page 34 of 85 |
| Date of Amendment: 15 Feb 2018 | EudraCT No.: 2012-000066-37 |                      |

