|  | 
syndrome, or ulcerative colitis and Crohn's disease.
 
 
13. History of unstable angina, coronary artery stenting or bypass grafting within three months of enrolment, transient ischemic attacks or stroke within four weeks of enrolment.
 
14. Prior chemotherapy or treatment with immunosuppressant drugs (azathioprine, chlorambucil, cyclophosphamide, or other alkylating agents), cyclosporine, etanercept, infliximab, interferon or any therapy with drugs known as ototoxic (e.g. aminoglycosides, cisplatin, loop diuretics, quinine etc.) in the past 6 months.
 
15. Gastrointestinal pathology: lesions liable to bleed such as active peptic ulcer disease, inflammatory bowel disease, history of gastrointestinal bleeding, or recent hemorrhage at any anatomical site requiring medical intervention.
 
16. Screening plasma fibrinogen level of <180 mg/dL.
 
17. Known disorder of platelet function or coagulation abnormality.
 
18. Platelet count of <100,000/mm^3.
 
19. Severe liver disease.
 
20. Hepatic failure (e.g., aspartate aminotransferase (SGOT) or alanine aminotransferase (SGPT) <math>\geq 3 \times</math> upper limit of normal [ULN])
 
21. Treatment with hyperbaric oxygen within one week prior to study drug.
 
22. Renal insufficiency (e.g., blood urea nitrogen or creatinine <math>\geq 2 \times</math> ULN) or patients on renal dialysis.
 
23. Use of another investigational drug within 30 days prior to SSDL onset.
 
24. Any other serious medical condition that might interfere with subject evaluation over the 90-day study period, based on the investigator's judgment, e.g. planned surgical intervention or any other condition which might give doubt for non-completing the study e.g. planned holiday, distance between investigational center and place of origin.
 
25. Known hypersensitivity to the drug substance or excipients.
 
26. Blood or blood product infusion within one week prior to study drug.
 
27. Use of any prohibited drug listed in chapter 6.4.1 and 6.4.2 of this study protocol.
 
28. Immunoglobulin infusion 4 weeks prior to study drug.
 
29. Planned treatment using intramuscular injections
 
 |

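### Exclusion 23 counts its 30 days back from hearing-loss onset, so a new investigational drug for another condition, outside the barred classes and started between onset and first dose, meets no exclusion

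*Combined protocol and SAP*

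**What the plan says.** Protocol 5.1.3, exclusion 23, reads "Use of another investigational drug within 30 days prior to SSL onset". The synopsis reads "Use of another investigational drug within 30 days prior to SSDL onset". Both anchor terms are evidently misspellings of SSHL, and both versions end the window at onset.

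Three statements fix the time from onset to dosing. Inclusion 4 in 5.1.2 says "Enrollment has to be accomplished within 7 days after SSHL onset". Section 4.1 says "All screening assessments including randomization and patient enrollment are to be performed within 36 hours", and then "Immediately after randomization, patients will receive the initial administration of study drug".

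The neighbouring criteria use other anchors. Exclusion 26, "Blood or blood product infusion within one week prior to study drug", counts back from study drug, as do 21 and 28. Exclusion 11, "Any pre-treatment within the preceding 30 days prior to screening, ongoing treatment or planned treatment of SSHL-related hearing loss", counts back from screening and also covers ongoing and planned treatment. Exclusion 27 bars "Use of any prohibited drug listed in chapter 6.4.1 and 6.4.2 of this study protocol". The two lists it points to name specific drug classes and procedures; neither names investigational drugs as a category.

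**The concern.** A washout rule for investigational drugs would normally protect the period just before the first dose, when an unknown interaction with the study drug is most likely to matter. This rule covers an earlier month and can leave the days closest to a defibrinogenating infusion open. Section 6.4.1 is also silent on investigational drugs during the study, so such an exposure could run on into the treatment week and overlap the Day 8 audiogram.

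Two things are at stake: the safety of the occasional patient who arrives with a recent experimental exposure, and a coherent eligibility rule. There is also a practical mismatch. The onset anchor can reach further back than the medication history that sites must record, while the recorded days nearest to dosing fall outside the rule.

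**Working it through.** The plan states no figure for this point, so there is none to reproduce. The check is date arithmetic, then a comparison of the rules that might close the gap.

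**1. Length of the gap.** Set first dose at day 0 and onset at day −d. Exclusion 23 covers day −(30 + d) to day −d, which leaves d days uncovered before dosing.

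| Onset to first dose, d | Exclusion 23 covers | Uncovered before dose |
|---|---|---|
| 0 days | −30 to 0 | 0 days |
| 3 days | −33 to −3 | 3 days |
| 7 days (inclusion 4) | −37 to −7 | 7 days |
| 8.5 days | −38.5 to −8.5 | 8.5 days |

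The last row applies only if the 7-day limit is taken at presentation, as Section 3.1 could be read, with the full 36 hours of screening added: 7 + 1.5 = 8.5. Inclusion 4 ties the limit to enrolment, so about 7 days is the working maximum.

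**2. Which other rules reach into the gap.**

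- Exclusion 11 bars any treatment of the hearing loss, investigational or not.
- Exclusion 14 bars chemotherapy, immunosuppressants and ototoxic drugs in the past 6 months.
- Exclusion 27, through 6.4.1 and 6.4.2, bars thrombolytics, anticoagulants, antiplatelet drugs, systemic corticosteroids and drugs that interfere with fibrinolysis, among others.
- Exclusion 23 itself catches a drug taken after onset if it was also used in the 30 days before onset.
- Withdrawal for meeting an exclusion criterion (5.1.4) does not help, because first use after onset can never meet a window that closed at onset.

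What remains is an investigational drug for another indication, outside the listed classes, first taken after onset (or resumed after a break of more than 30 days ending at onset).

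**3. Reach compared with the record.** Section 4.1 and note c of Appendix 17.6 require medication from the 30 days before Visit 1. At d = 7 the rule starts at day −37. If Visit 1 falls on the dosing day, the record starts at day −30, so 37 − 30 = 7 days of the window lie outside it. If screening began 36 hours before dosing, the record starts at day −31.5 and 37 − 31.5 = 5.5 days lie outside it.

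**4. Effect on the Day 8 comparison.** SAP Section 2 expects only a few more than 30 evaluable patients. As an assumption, take 30 to 40 patients randomized 2:1. Suppose one affected ancrod patient lies 20 dB from the mean, which is one planned standard deviation. The shift in the arm mean is 20/n, and the standard error of the difference is 20 × √(1/n₁ + 1/n₂).

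| Ancrod, placebo | Shift in ancrod mean | Standard error | Ratio |
|---|---|---|---|
| 20, 10 | 20/20 = 1.0 dB | 20 × √0.150 = 7.7 dB | 13% |
| 24, 12 | 20/24 = 0.83 dB | 20 × √0.125 = 7.1 dB | 12% |
| 27, 13 | 20/27 = 0.74 dB | 20 × √0.114 = 6.8 dB | 11% |
| 66, 33 (planned) | 20/66 = 0.30 dB | 20 × √0.0455 = 4.3 dB | 7% |

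Against the 15 dB target, 0.83 dB is 0.83/15 = 5.5%.

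**The case against.** The strongest reply is that the remaining case hardly ever arises: within a week of sudden hearing loss, a patient would have to start an experimental drug for something unrelated and outside every listed class. Nothing in the documents suggests that this happened. That stands, and it keeps the point minor.

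Second, no single convention is broken. Exclusion 13 counts from enrolment and exclusion 14 names no anchor event. An onset anchor might also be meant to keep out hearing loss caused by an experimental drug. That is possible, but the protocol gives no such reason, and the purpose would not require the window to stop at onset.

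Third, medication is recorded at every visit, and SAP Section 4.5 already provides listings for checking medications at the blind data review. This stands in part. The data should be there, but a drug that no rule prohibits is not clearly a deviation, so only the general clause on other circumstances would catch it. That clause affects the Per Protocol Set only, not the primary Full Analysis Set.

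A reader might go further and infer that any investigational drug is allowed between onset and dosing, or that one still in use at dosing escapes every rule. The documents do not support either reading: exclusions 11, 14 and 27 bar much of this use, and a drug continued from before onset already meets exclusion 23. A reader might also infer bias in the Day 8 result. Exposure before randomization cannot depend on the blinded allocation, so it adds noise, and little of it.

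**Conclusion.** The gap is real but narrow. Exclusion 23 leaves 0 to about 7 days before the first dose uncovered for one kind of exposure: a newly started investigational drug for another indication, outside the classes barred elsewhere. Section 6.4.1 does not address that category during the study either. The anchor is out of step with exclusions 21, 26 and 28 (study drug) and with exclusion 11 and the 6.4.1 look-backs (screening). At the 7-day limit it also reaches some 5.5 to 7 days beyond the required medication history.

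This is a minor, worthwhile correction. Its value lies in safety and consistent eligibility; no material change to the Day 8 estimate should be expected. The length of the gap follows from the documents. The arm sizes of 20 to 27 and the single patient 20 dB from the mean are assumptions. The judgement that very few patients are affected is also an assumption, since no count is given.

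**What to change.** In Section 5.1.3 and the synopsis, word exclusion 23 so that the window runs without a break up to dosing, for example: use of another investigational drug at any time from 30 days before SSHL onset until first study drug. Correct 'SSL' and 'SSDL' to SSHL at the same time. State whether the silence of 6.4.1 on investigational drugs during the study is intended. Add investigational drugs to the medication check at the blind data review.

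Simply moving the 30 days to end at study drug would also close the gap and would fit the recorded history better. It would, however, make eligible some patients who are now excluded: at d = 7, those whose use ended 31 to about 37 days before dosing. Keeping the pre-onset window avoids that, but sites then need to ask directly about investigational drugs back to 30 days before onset.

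The cost is a few words, but they change eligibility, so Section 13.2 requires ethics committee and competent authority approval. The synopsis plans last treatment for July 2018 and few further patients are expected. If recruitment is too far on for an amendment, the data-review check alone can still be made before database lock, at the cost of one listing.
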